## **2.4 Sample size calculation**

This study will use a superiority design. According to the pilot study, the incidence rate of urinary retention was 7.7% in the intervention group and 25.7% in the control group. Assuming a 1 : 1 ratio of intervention to control group and using a one-sided test, a significance level ( $\alpha$ ) of 0.025 and a power ( $1-\beta$ ) of 80% and a possible drop-out rate of 20%, the estimated sample size is 600 cases in each group with 50 cases at each center in each group. Intervention and control groups would require a total sample size of 1200 cases.

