### 2.8.2 Secondary outcomes

Postpartum uterine contraction pain: The visual analogue scale (VAS) will be used to evaluate the postpartum uterine contraction pain intensity: Using a horizontal ruler of 100 mm, “0” representing no pain and “100” representing unbearable pain. The pain VAS intensity will be respectively measured at  $6 \pm 0.5$  hours,  $28 \pm 0.5$  hours,  $52 \pm 0.5$  hours, and  $76 \pm 0.5$  hours after delivery.

Emotion symptoms: The Edinburgh Postnatal Depression Scale (EPDS) will be used for screening the depressive symptoms at  $76 \pm 0.5$  hours after delivery. It contains 10-item: pessimism, lack of interest, self-blame, worry, fear, impaired ability, sleep disorder, sadness, tearfulness, self-injury/suicidal ideation, each of which is scored from 0 to 3.

Lactation: The lactation initiation time will be recorded, and the breastfeeding milk volume, feeding mood and times, and the newborn weight will be measured at  $28 \pm 0.5$ ,  $52 \pm 0.5$ , and  $76 \pm 0.5$  hours after delivery, respectively. The breastfeeding milk volume is measured as “-” to “++++”: no milk outflow during finger extrusion(-); milk occasionally flows out during finger extrusion, which cannot meet the needs of the infants (+); milk flows out slowly when squeezed by fingers but does meet the needs of infants (+ +); milk continuously flows out during finger extrusion, which can meet the needs of infants (+ + +); there is milk flowing out in a jet shape when the nipple is squeezed by the fingers, which can meet the needs of infants (+ + + +).

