## **2. Analysis Software**

Statistical analysis will be performed by independent analysts by R (version 4.1.0; R Development Core Team) software. All hypothesis testing will be carried out at the 5% (2-sided) significance level.

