## 6. Analyses for Secondary Outcome

For the secondary outcomes, the changes of postpartum uterine contraction pain assessing with Visual Analogue Scale Score at  $6\pm0.5$ ,  $28\pm0.5$ ,  $52\pm0.5$  and  $76\pm0.5$  hours after birth will be analyzed by fitting a linear mixed model using treatment, time, treatment by time interaction as a fixed effect, the comparison between the two groups at each time-point will be performed using linear regression model.

The emotion symptoms screening by the Edinburgh Postnatal Depression Scale Score will be compared using a logistic regression model.

The lactation initiation time will be compared using the Wilcoxon rank-sum test. The changes of breastfeeding milk volume, feeding mood and feeding times at  $28\pm0.5$ ,  $52\pm0.5$  and  $76\pm0.5$  hours after birth will be analyzed by a generalized linear mixed model. The difference of breast feeding milk volume and feeding times between two groups at each time-point will be analyzed by an ordinal logistic regression model, and feeding mood will be analyzed by a logistic regression model. The changes of newborn weight at  $28\pm0.5$ ,  $52\pm0.5$  and  $76\pm0.5$  hours after birth will be analyzed by fitting a linear mixed model using treatment, time, treatment by time interaction as a fixed effect, the comparison between the two groups at each time-point will be performed using a linear regression model.

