## 9. Changes to the original analysis plan

As compared to the initial statistical analysis plan (SAP) published in Clinical and Experimental Obstetrics & Gynecology([name], [name], Chang Liu, Nicola Robinson, Myeong Soo Lee, Xiaoyang Mio Hu, Hye Won Lee, Rong Zhang, [name]\*. Effectiveness of acupoint hot compress on early puerperal rehabilitation of parturients after natural childbirth: study protocol for a prospective, multi-center, randomized controlled clinical trial. Clinical and Experimental Obstetrics & Gynecology. 2021;48(6):1350-1357), the original analysis plan has been amended as follows:

Based on the preliminary analysis of the available data, we found spinal analgesia may have potential effects on the outcomes, a subgroup analysis was then conducted.

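### The EPDS total (0-30) has no planned between-group analysis, and the logistic comparison that replaces it has no stated cut-off

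*Supplement*

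**What the plan says.** Protocol section 2.8.2 introduces the EPDS as a 10-item scale that "will be used for screening the depressive symptoms at" 76 ± 0.5 hours after delivery, with items "each of which is scored from 0 to 3". It gives no threshold for a positive screen.

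SAP section 6 has one sentence on its analysis: "The emotion symptoms screening by the Edinburgh Postnatal Depression Scale Score will be compared using a logistic regression model". It names no event, cut-off or effect measure.

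The same section uses linear models for VAS pain and newborn weight. For lactation it separates two kinds of logistic model: milk volume and feeding times "will be analyzed by an ordinal logistic regression model, and feeding mood will be analyzed by a logistic regression model". SAP section 5 also uses a plain logistic model for the yes/no primary outcome, and there it does name an effect measure, the relative risk.

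Protocol section 7 has general text on t tests and rank tests for continuous data. It does not mention the EPDS and refers to the SAP for detail.

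**The concern.** The EPDS is the only listed outcome behind the objective of preventing emotional disorders (protocol section 2.3.1). Two things are at stake.

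- **The endpoint is not defined.** Two analysts following SAP section 6 could choose different cut-offs and report different results. Nothing in the text would show which one was planned.
- **Information is discarded.** The other outcomes measured on a numeric scale, pain and newborn weight, keep their full scale. The EPDS appears to be reduced to two categories, with no analysis of the total beside it and no reason given.

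**Working it through.** **Is the comparison yes/no?** The SAP writes ordinal logistic where it means ordered categories and plain logistic for the binary primary outcome. Plain logistic for the EPDS therefore most naturally means a dichotomy. This is a strong inference, not an explicit statement. If an ordinal model was meant, the sentence still needs correcting.

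**The plan's own figures.** None is given for the EPDS. The sample size (protocol section 2.4) was set for urinary retention: "the estimated sample size is 600 cases in each group with 50 cases at each center in each group". I use it only for scale. With the stated 20% drop-out, 600 × 0.8 = 480 evaluable women per group. The test level is 5% two-sided (SAP section 2).

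**Information lost by a split.** For a small shift in a normal score, the efficiency of a yes/no split relative to the mean is φ(c)² / [p(1 − p)]. Here p is the share above the cut-off, c the matching normal quantile and φ the normal density.

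- p = 0.50: 0.3989² / 0.25 = 0.637
- p = 0.20: 0.2800² / 0.16 = 0.490
- p = 0.05: 0.1031² / 0.0475 = 0.224

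For the power column, the standardised difference that gives the full score 80% power with 480 per group is (1.960 + 0.842) × √(2/480) = 0.181.

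| Share positive (assumed) | Efficiency | Information lost | Power of the split when the full score has 80% |
|---|---|---|---|
| 50% | 0.637 | 36% | 61% |
| 30% | 0.576 | 42% | 55% |
| 21% | 0.501 | 50% | not computed |
| 20% | 0.490 | 51% | 48% |
| 15% | 0.426 | 57% | 42% |
| 10% | 0.342 | 66% | 34% |
| 5% | 0.224 | 78% | 24% |

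**Skewed scores.** EPDS totals are unlikely to be normal, so two assumed skewed distributions were simulated, each at cut-offs 9 to 13. Power converts to relative efficiency as [(1.96 + z for the split's power) / (1.96 + z for the mean's power)]².

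- *Rounded-down gamma* (mean 5.5 and SD 4 before rounding, values 12% lower on treatment). With 480 per group, power was 76% for the mean and 38-55% for single cut-offs, an efficiency of 0.39-0.61. With 600 per group it was 86% against 46-64%, an efficiency of 0.37-0.58.
- *Negative binomial capped at 30* (mean 5-7, SD 4-4.5, 480 per group). Power was about 85% for the mean and 53-69% for single cut-offs. The extremes convert to (2.025/3.009)² = 0.45 and (2.467/3.005)² = 0.67.

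The loss across both is about one third to three fifths.

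**Leaving the cut-off open.** With no treatment effect, the chance that at least one of the cut-offs 9 to 13 gives p < 0.05 was 12.5% and 13.4% in the first model (480 and 600 per group), and 13.4-13.8% in the second. Five independent tests would give 1 − 0.95⁵ = 22.6%. Adjacent cut-offs overlap heavily, so the figure is lower, but it is still more than twice the nominal 5%.

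**The case against.** **A screening proportion fits the purpose.** The protocol uses the EPDS to screen, and its objective is prevention. A proportion screening positive answers that directly, whereas a mean shift among mostly low scorers answers a different question. This stands. It is a reason to keep the logistic comparison, but not to leave its cut-off blank or the total uncompared.

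**The loss may be less than half.** A reader might infer that half or more of the information must go. The documents do not support that: it requires about 21% or fewer to screen positive, and no rate is given. The exclusion of mental illness and of a family history of it (protocol section 2.3.5.2) makes a low rate plausible, but nothing in the documents links those criteria to symptoms at 76 hours.

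**A real effect need not be missed.** A reader might also infer that a true shift would probably go undetected. In the gamma model the best cut-off still had 55% power (480 per group) or 64% (600 per group).

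**No evidence of a chosen cut-off.** SAP section 9 records a change made "Based on the preliminary analysis of the available data", which might suggest that the EPDS cut-off was chosen the same way. That change concerns a spinal-analgesia subgroup. The section does not mention the EPDS or say that the look was by arm. Protocol section 2.5 blinds outcome assessors and statisticians to allocation. This lowers the risk, but blinding does not define an endpoint.

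**Conclusion.** The point holds as a gap in a secondary analysis. SAP section 6 gives the EPDS one comparison, in context yes/no, with no cut-off or effect measure, and the total has no planned between-group analysis.

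For a normal score the loss runs from about 36% at a median split to about 78% if 5% screen positive. Where the trial falls in that range cannot be told from the documents. The 12-14% false-positive rate is a worst case. It assumes particular score distributions, five candidate cut-offs, and a choice of the best after seeing results by arm. The primary conclusion on urinary retention does not depend on any of this.

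**What to change.** In SAP section 6:

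- Add a between-group comparison of the EPDS total at 76 hours, by linear regression with robust standard errors or by a proportional-odds model, with a 95% CI.
- Keep the logistic screening comparison at one cut-off. Write that cut-off and the effect measure into the SAP before unblinding.
- If the change is made after the preliminary look at the data described in SAP section 9, date it and say so.

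No new data are needed. The cost is one more secondary analysis, and a mean difference is less directly a screening result than a proportion; the retained fixed cut-off comparison covers that. The SAP should also say which of the two is read first, since each would otherwise be tested at 5%.

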## 11. Update on the Published Protocol

As compared to the published protocol ([name], [name], Chang Liu, Nicola Robinson, Myeong Soo Lee, Xiaoyang Mio Hu, Hye Won Lee, Rong Zhang, [name]\*. Effectiveness of acupoint hot compress on early puerperal rehabilitation of parturients after natural childbirth: study protocol for a prospective, multi-center, randomized controlled clinical trial. *Clinical and Experimental Obstetrics & Gynecology*.2021;48(6):1350-1357), the present study protocol has made several amendments.

- (1) The medical provision of two centers changed, which has limited the number of the available participants with inclusion criteria of the study, and these two centers were not included in the trial.
- (2) The analysis used in the present trial is referred to as an “per protocol” analysis.
- (3) To detect the effects of acupoint hot compress on reducing the incidence of urinary retention more accurately, we used a broader standard to identify postpartum urinary retention.
- (4) To detect the effects of acupoint hot compress on lactation, we used a detailed measurement to quantify the breastfeeding milk volume.
- (5) As all the outcomes collected from 6±0.5 hours to 76±0.5 hours after delivery, the changes of maternal weight is tiny, so the weight was not included in the analysis.

**Effects of acupoint hot compress during early puerperium on parturients after a vaginal delivery: study protocol for a randomized clinical trial**

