## **1. Study Populations**

All subjects with randomization will be included in the analysis set regardless of whether they receive any treatment. According to the intention-to-treat principle, all analysis will be based on the randomization set.

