## **3. Missing Data**

Missingness is considered to be missing at random (MAR) and multiple imputation (MI) techniques will be used for handling missing data.

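### The SAP gives no rule for a woman who has not started lactating by 76 hours, and its only rule for absent values, MAR imputation, does not suit her

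*Supplement*

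**What the plan says.** Protocol section 2.8.2 lists lactation among the secondary outcomes and states "The lactation initiation time will be recorded". It gives no definition of initiation and no rule for a woman in whom it has not occurred. The last column of the assessment schedule (Figure 1) is 76±0.5 hours, and protocol section 11 confirms the window: "As all the outcomes collected from 6±0.5 hours to 76±0.5 hours after delivery". The milk-volume scale in section 2.8.2, scored at 28, 52 and 76 hours, has a lowest grade described as "no milk outflow during finger extrusion", so the protocol itself allows for women without milk at the last visit.

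SAP section 6 gives the whole analysis of the initiation time in one sentence: "The lactation initiation time will be compared using the Wilcoxon rank-sum test". SAP section 1 keeps every randomised woman: "According to the intention-to-treat principle, all analysis will be based on the randomization set". SAP section 3 is the only text on absent values: "Missingness is considered to be missing at random (MAR) and multiple imputation (MI) techniques will be used for handling missing data". It names no imputation model and no exception.

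**The concern.** This is a time to an event with observation stopped at a fixed point. A woman not started at the last visit has no time to record, but her result is not unknown: it is later than 76 hours. Her time is absent because of its own value, and an ordinary MAR imputation does not represent that.

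An analyst following the SAP literally meets an empty field, an instruction to analyse all randomised women, and an instruction to impute. Unless the imputation is told that the time must exceed 76 hours, it will draw largely on women who started earlier. Leaving her out instead loses the same information. Either way, the latest results are the ones affected.

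Promoting lactation is one of the four aims in protocol section 2.3.1, and this is the only outcome that measures its timing. An unwritten rule can also be settled after the data have been seen.

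**Working it through.** **Is there a planned figure to reproduce?** No. The 600 per group in protocol section 2.4 is for urinary retention. The documents give no median, effect size, power or non-initiation rate for lactation, so everything below is conditional on assumptions.

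**Inputs from the documents.** Cut-off 76 hours in both arms; two-sided 5% level (SAP section 2); 600 per arm less 20% drop-out (section 2.4), so 600 × (1 − 0.20) = 480 per arm.

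**Assumptions.** Control times are log-normal with log-SD 0.6. The location is set so that a share p of controls has not started by 76 hours: μ = ln 76 − 0.6 × z(1−p). The intervention speeds onset with hazard ratio 1.2: S_T(t) = S_C(t)^1.2. For p = 10%, μ = 4.331 − 0.6 × 1.282 = 3.562, a control median of about 35 hours, and the intervention arm has 0.10^1.2 = 6.3% not started. In numbers of control women out of 480, 1%, 5% and 10% are about 5, 24 and 48.

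**Analyses compared (600 simulated trials per row).** (a) Wilcoxon with non-starters dropped; (b) Wilcoxon with non-starters filled by one draw from observed times in the same arm, a crude stand-in for MAR imputation; (c) Wilcoxon with non-starters tied at the longest rank; (d) log-rank censored at 76 hours.

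| Controls not started | (a) dropped | (b) filled | (c) tied longest | (d) log-rank | (c) − (a) |
|---|---|---|---|---|---|
| 1% | 0.612 | 0.613 | 0.663 | 0.800 | 0.051 |
| 2% | 0.627 | 0.625 | 0.703 | 0.817 | 0.076 |
| 5% | 0.480 | 0.503 | 0.690 | 0.802 | 0.210 |
| 10% | 0.393 | 0.432 | 0.707 | 0.800 | 0.314 |
| 20% | 0.230 | 0.295 | 0.635 | 0.705 | 0.405 |
| 30% | 0.148 | 0.227 | 0.648 | 0.698 | 0.500 |

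The Monte Carlo standard error of a power near 0.5 is √(0.5 × 0.5 / 600) = 0.020. A separate simulation with 480 per arm and the same hazard ratio gave (a) against (c) of 0.64 against 0.68 at 1%, 0.51 against 0.71 at 5%, and 0.37 against 0.68 at 10%: differences of 4, 20 and 31 points.

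Columns (a) and (c) use the same test, so their difference isolates the handling of non-starters. The log-rank column is favoured here because the simulated effect has proportional hazards. With no effect, (a), (c) and (d) rejected in 4% to 7% of trials. Column (b) rejected in 12.5% and 14.5% at 20% and 30% not started. That is an artefact of a single draw and is not attributed to the SAP.

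**Direction.** Two other patterns were tried, each moving half of the intervention arm's non-starters to a time before 76 hours.

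- *Moved to typical observed times.* The dropped analysis rejects in 5.2% of trials at 10% not started and 6.8% at 20%, so it sees almost nothing. Tied longest gives 26.5% and 79.2%; log-rank gives 61.8% and 97.0%.
- *Moved to between 60 and 76 hours.* The dropped analysis now points towards control: median difference (control minus intervention) −1.33 hours at 10% and −3.11 hours at 20%. Tied longest rejects in 4.7% and 13.2%; log-rank in 21.3% and 64.5%.

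A real benefit can therefore be weakened, missed or reversed in appearance, depending on its form.

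**The case against.** The strongest reply is that the SAP is silent rather than wrong. A reader might infer that the plan drops women who have not started, or gives them an early start time, and so hides a benefit. The documents do not say this. SAP section 6 names a test and nothing more; SAP section 1 keeps all randomised women, so dropping would go against it; SAP section 3 does not say that not having started counts as missing. Nor does it name an imputation model: one that used the milk grades, or drew only times beyond 76 hours, need not give an early time. This stands. What remains is that the only written rule for an empty field is MAR imputation, and nothing excludes these women from it.

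A reader might also infer that the Wilcoxon test is unsuitable. It is not. With a cut-off common to both arms, non-starters can share the longest rank and the test is valid.

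Nor would an effect on non-starting go unseen across the trial. Milk volume, including its lowest grade, is analysed at 28, 52 and 76 hours by ordinal logistic regression and a generalised linear mixed model, and fewer women without milk at 76 hours should show there. The timing outcome would still be affected.

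The share not started is an assumption. Initiation is undefined, and breastfeeding is an inclusion criterion, so the share could be very small. This also stands, and it limits the size of the point.

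Finally, censoring early leavers at exit assumes that leaving is unrelated to when lactation would have started, an assumption of the same kind as MAR. Some of the exits in protocol section 2.3.5.4, such as haemorrhage or neonatal transfer, make it debatable. The case is clear for women followed to 76 hours and weaker for those who leave before.

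**Conclusion.** The point holds as a gap combined with an ill-suited default: no rule for a woman known to exceed 76 hours, and one rule for absent values that does not represent what is known about her. It concerns one component of a secondary outcome and does not touch the primary comparison.

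Under the proportional-hazards assumptions shown above, the power lost by dropping non-starters instead of ranking them last is about 4 to 5 points if 1% of controls have not started, about 20 at 5% and about 30 at 10%; it is zero if everyone has started. The single-draw fill-in loses a similar amount at 5% and 10% (0.690 − 0.503 = 0.187 and 0.707 − 0.432 = 0.275), but it only approximates what a multiple imputation would do.

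The documents do not support a fixed direction. A reader might infer that any bias runs toward no difference; the second pattern above shows that it can favour control.

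**What to change.** In SAP section 6, state that a woman not started by 76 hours is not treated as missing and is kept out of the MAR imputation. Then specify one of two analyses:

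- **Time to event.** Measure from delivery; right-censor non-starters at 76 hours and early leavers at their last assessment, stating the assumption of non-informative exit. Show Kaplan-Meier curves and use a log-rank test, adding a Cox hazard ratio with 95% CI if proportional hazards is reasonable.
- **Wilcoxon retained.** Rank all women not started by 76 hours as tied longest. Early leavers have no common cut-off, so this option needs its own stated rule for them.

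Under either option, report the number not started at 76 hours by arm, so that readers can judge how much the choice matters.

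The cost is a few sentences in the SAP and a few lines of R, with no new data. The one real price is the non-informative censoring assumption for early leavers.

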## 7. Subgroup analysis

To consider the potential effects of labor analgesic drug use on the outcomes, a subgroup analysis will be conducted according to whether medication is used for labor analgesia or not. The subgroup RRs and 95% CIs will be calculated together with interaction P values.

## 8. Safety Analysis

Adverse event listings will be generated and events will be classified according to seriousness, treatment relationship and resolution. Descriptive statistics (numerical measures, frequency tables) will be used to summarize the occurrence of adverse events and serious adverse events by intervention group.

## 9. Changes to the original analysis plan

As compared to the initial statistical analysis plan (SAP) published in Clinical and Experimental Obstetrics & Gynecology([name], [name], Chang Liu, Nicola Robinson, Myeong Soo Lee, Xiaoyang Mio Hu, Hye Won Lee, Rong Zhang, [name]\*. Effectiveness of acupoint hot compress on early puerperal rehabilitation of parturients after natural childbirth: study protocol for a prospective, multi-center, randomized controlled clinical trial. Clinical and Experimental Obstetrics & Gynecology. 2021;48(6):1350-1357), the original analysis plan has been amended as follows:

Based on the preliminary analysis of the available data, we found spinal analgesia may have potential effects on the outcomes, a subgroup analysis was then conducted.
